## 4. STUDY POPULATION

### 4.1 Population (base)

In this prospective cohort study, eligible pregnant patients (N=60) will be included. See sections 4.2 and 4.3 for inclusion and exclusion criteria, and Table 1 for definitions.

### 4.2 Inclusion criteria

In order to be eligible to participate in this study, a subject must meet all of the following criteria:

- Minimum age of 18 years old
- Pregnant patients with a gestational age between 32+0 and 36+6 weeks and days
- Singleton pregnancy
- Any indication for fetal monitoring at least twice per week (e.g.):
  - PE
  - FGR
  - PPRM
- Absence of exclusion criteria > 24 hours after admission.
- Oral and written informed consent is obtained.

### 4.3 Exclusion criteria

A potential subject who meets any of the following criteria will be excluded from participation in this study:

- An indication for intravenous medication
- Blood pressure >160/110mmHg
- Absent-/or reversed flow umbilical artery Doppler
- HELLP (Table 1)
- Obstetric intervention expected <48 hours, e.g. due to:
  - Non reassuring CTG
  - Active vaginal blood loss
  - Signs of abruption placentae
  - Meconium stained amniotic fluid
  - Signs of chorioamnionitis
- Patients admitted with a clinical diagnosis of sepsis with hypotension (i.e. septic shock).
- Insufficient knowledge of Dutch or English language
- Insufficient comprehension of instruction Nemo Remote® or patient information
- Fetal and/or maternal cardiac arrhythmias
- Contraindications to abdominal patch placement (dermatologic diseases of the abdomen precluding preparation of the abdomen with abrasive paper)
- Patients connected to an external or implanted electrical stimulator, such as Transcutaneous Electro Neuro Stimulation (TENS) and pacemaker (because of disturbance of the electrophysiological signal).

*Table 1. Definitions of pregnancy related diagnosis*

|                                                                                                                                                                                                                                                                                                                                                                                                                                                                                                                                                                                                                                                                                                                                                                                                                                                                                                                                                                                                                                                                           |
|---------------------------------------------------------------------------------------------------------------------------------------------------------------------------------------------------------------------------------------------------------------------------------------------------------------------------------------------------------------------------------------------------------------------------------------------------------------------------------------------------------------------------------------------------------------------------------------------------------------------------------------------------------------------------------------------------------------------------------------------------------------------------------------------------------------------------------------------------------------------------------------------------------------------------------------------------------------------------------------------------------------------------------------------------------------------------|
| Pre-eclampsia (PE)                                                                                                                                                                                                                                                                                                                                                                                                                                                                                                                                                                                                                                                                                                                                                                                                                                                                                                                                                                                                                                                 |
| 
Pre-eclampsia is pregnancy induced hypertension (PIH) accompanied by one or more of the following new-onset conditions at or after 20 weeks' gestation (26):
 
 
1. Proteinuria
 
2. Other maternal organ dysfunction, including: 
 
o Acute kidney injury (AKI) (creatinine <math>\geq 90 \mu\text{mol/L}</math>; 1 mg/dL)
 
o Liver involvement (elevated transaminases e.g. ALT or AST <math>> 40 \text{ IU/L}</math>) with or without right upper quadrant or epigastric abdominal pain)
 
o Neurological complications (examples include eclampsia, altered mental status, blindness, stroke, clonus, severe headaches, persistent visual scotomata)
 
o Haematological complications (thrombocytopenia – platelet count below 150,000/<math>\mu\text{L}</math>, DIC, hemolysis)
 
 
 
3. Uteroplacental dysfunction (such as fetal growth restriction, abnormal umbilical artery Doppler wave form analysis, or stillbirth).
 
 |
| Fetal growth restriction (FGR)                                                                                                                                                                                                                                                                                                                                                                                                                                                                                                                                                                                                                                                                                                                                                                                                                                                                                                                                                                                                                                     |
| 
Fetuses with an estimated fetal weight (EFW) or abdominal circumference (FAC) that is less than the 10th percentile for gestational age (27).
                                                                                                                                                                                                                                                                                                                                                                                                                                                                                                                                                                                                                                                                                                                                                                                                                                                                                                                      |
| Preterm pre-labor rupture of membranes (PPROM)                                                                                                                                                                                                                                                                                                                                                                                                                                                                                                                                                                                                                                                                                                                                                                                                                                                                                                                                                                                                                     |
| 
Rupture of membranes before gestational age of 37 weeks without contractions (11).
                                                                                                                                                                                                                                                                                                                                                                                                                                                                                                                                                                                                                                                                                                                                                                                                                                                                                                                                                                                 |
| HELLP syndrome (Haemolysis Elevated Liver enzymes and Low Platelets)                                                                                                                                                                                                                                                                                                                                                                                                                                                                                                                                                                                                                                                                                                                                                                                                                                                                                                                                                                                               |
| 
The combination of all or some of haemolysis elevated liver enzymes and thrombocytopenia (26). Combination of symptoms that signifies a more serious manifestation of PE.
 
 
* Haemolysis (LDH <math>\geq 600 \text{ U/L}</math>, haptoglobin <math>< 0.2 \text{ g/L}</math> AND
 
* Elevated liver enzymes (ASAT or ALAT <math>> 70 \text{ U/L}</math>) AND
 
* Low platelets (<math>< 100 \times 10^9/\text{L}</math>).
 
                                                                                                                                                                                                                                                                                                                                                                                                                                                                                                                                                                    |

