### ***Patient satisfaction parameters***

To assess patient wellbeing and satisfaction, all included patients will receive the following validated (31) questionnaires through Research Manager®. At the first day of inclusion the EQ-5D-5L including VAS (31), before discharge the D-QUEST (35) and at 4 weeks after delivery EQ-5D-5L including VAS and CSQ-8 (31) questionnaires (7.3.3). The questionnaires can be digitally completed in on average 3-10 minutes. All surveys are attached as appendix ( A, B and C). The analysis is described in section 9.2.1.

- At inclusion: EQ-5D-5L (36) including EQ VAS (visual analogue scale). Questionnaire assessing the effect of the eCTG on patients health/wellbeing. The descriptive system comprises the following five dimensions: mobility, self-care, usual activities, pain/discomfort and anxiety/depression. Each dimension has five response levels: no problems, slight problems, moderate problems, severe problems, unable to /extreme problems. The participants are asked to indicate her health state by checking the box next to the most appropriate response level for each of the five dimensions. Responses are coded as single-digit numbers expressing the severity level selected in each dimension. The EQ VAS records the respondent's overall current health on a vertical visual analogue scale, where the endpoints are labelled 'The best health you can imagine' and 'The worst health you can imagine'. The EQ VAS provides a quantitative measure of the patient's perception of their overall health.
- Discharge: Satisfaction patient regarding the use of the eCTG D-QUEST (35) Dutch version of the Quebec User Evaluation of Satisfaction with assistive Technology.
- At 4 weeks after delivery: Satisfaction regarding the effect of the eCTG on their health/wellbeing EQ-5D-5L (36) including VAS (visual analogue scale) + satisfaction CSQ-8 (client/patient satisfaction questionnaire) (31).

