## **7.3 Study procedures**

### **7.3.1 Selection, counseling and inclusion**

An overview of the study procedure is integrated in the flowchart presented in chapter 3.

Eligible patients are identified at admission or at the outpatient clinic if an indication for monitoring at least twice a week is set (1st day). All eligible patients will be consecutively asked if they agree to receive information about the study by the attending gynaecologist or resident. They will receive verbal and written information (patient information folder (PIF)) in Dutch or English about remote eCTG monitoring in a Home@Hospital setting. The information will be provided by another (trained) attending obstetric health care professional (resident, physician assistant (PA), (research) midwife or nurse). Possible further questions will be answered and counselling will be performed by one of the researchers or their delegates (trained and registered in a delegation log). Procedure as prescribed above, will ensure that patients' participation will not be influenced by a dependent factor. Additionally, a brochure 'Wetenschappelijk onderzoek' will be assigned to the patient in 'mijnmmc' account – available for all patients – to provide general information about participation in scientific research. Patients will have 24 hours to decide if they want to participate in the study. After 24 hours (2nd day) – when still eligible – patient will provide informed consent and will receive a hard copy of the informed consent form. Given the nature of the study and the study population, it is necessary to deviate from standard Dutch regulations where a minimum reflection period of 7 days is required. This study concerns high-risk pregnant women where the delivery can take place within a short period of time (within a few days). In addition, to answer the research question, it is of great importance that fetal monitoring is examined early after diagnosis so the sample size of 60 participants will be achieved. Patients will be free to ask more time to think about it. When they meet the inclusion and exclusion criteria a few days after admission, it is still possible to participate in the study. Patients who are monitored on an outpatient basis have extra time to think about it until the next outpatient appointment if necessary.

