### **7.3.2 Interventions**

Participants at the clinic will self-administer remote eCTG monitoring with the NRM (Figure 1) and will enter their self-performed measurements, symptoms and vital functions in the Luscii® app. For detailed description of the objectives and interventional treatment, see sections 2.1, 2.2 and 5.1. For an overview of the study interventions see Figure 12. Initially, patient' appointment at the outpatient clinic may be extended by 5 minutes due to the self-administered eCTG measurement, but ultimately the self-administered measurement probably will save time for the participants because there will be no waiting time for the HCP.

Participants will receive a Quick Start Guide (QSG) and for HCPs an Information For Users (IFU) manual of NRM will be available. Both manuals will be available at the ward and published on the local study website at the MMC. Documents will be added to the clinical trial management system (CTMS) in Research Manager® (NRM-QSG-NL\_v2, NRM-IFU-NL v2).

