#### **Tevredenheid over uw hulpmiddel en de bijbehorende dienstverlening**

Het doel van deze vragenlijst is na te gaan hoe tevreden u bent over uw hulpmiddel en de bijbehorende dienstverlening.

- Wilt u bij elk van de vragen aangeven hoe tevreden u bent over uw hulpmiddel en de bijbehorende dienstverlening, met behulp van de volgende 5 antwoord-mogelijkheden:

Totaal niet tevreden  
Niet tevreden  
Min of meer tevreden  
Tevreden  
Zeer tevreden

- Wilt u alstublieft voor elk van de volgende vragen het antwoord aankruisen dat het best bij uw mate van tevredenheid past?
- Wilt u alstublieft alle vragen beantwoorden?
- Indien u niet helemaal tevreden bent, wilt u dan alstublieft de reden daarvan toelichten in de daarvoor bestemde ruimte achter de vraag?

|                                                                    |                                                                                                                              |                                                                                            |                       |
|--------------------------------------------------------------------|------------------------------------------------------------------------------------------------------------------------------|--------------------------------------------------------------------------------------------|-----------------------|
| 1                                                                  | Hoe tevreden bent u over de afmetingen van uw hulpmiddel?
(maat, hoogte, lengte, breedte)                                 | Totaal niet tevreden
Niet tevreden
Min of meer tevreden
Tevreden
Zeer tevreden | Reden ontevredenheid: |
| 2                                                                  | Hoe tevreden bent u over het gewicht van uw hulpmiddel?                                                                      | Totaal niet tevreden
Niet tevreden
Min of meer tevreden
Tevreden
Zeer tevreden | Reden ontevredenheid: |
| 3                                                                  | Hoe tevreden bent u over de verstel-mogelijkheden van uw hulpmiddel?                                                         | Totaal niet tevreden
Niet tevreden
Min of meer tevreden
Tevreden
Zeer tevreden | Reden ontevredenheid: |

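### Women who know English but not Dutch are eligible, yet the only patient questionnaire on satisfaction with the eCTG device is assigned in its Dutch version

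*Protocol*

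**What the plan says.** Eligibility is open to speakers of either language. Section 4.3 excludes "Insufficient knowledge of Dutch or English language", so one of the two is enough. Section 7.3.1 shows that this is intended: "They will receive verbal and written information (patient information folder (PIF)) in Dutch or English".

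Section 7.1.2 sends the questionnaires to all included patients. The discharge instrument is "D-QUEST (35) Dutch version of the Quebec User Evaluation of Satisfaction with assistive Technology". Appendix B prints it in Dutch and opens with "Het doel van deze vragenlijst is na te gaan hoe tevreden u bent over uw hulpmiddel en de bijbehorende dienstverlening". No other language version is mentioned in sections 7.1.2, 7.3.3 or 9.2.1.

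On device instructions, section 7.3.2 states "Participants will receive a Quick Start Guide (QSG) and for HCPs an Information For Users (IFU) manual of NRM will be available". The files it names for the trial management system carry NL in their names ("Research Manager® (NRM-QSG-NL"); no English file is listed.

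The EQ-5D-5L with its visual analogue scale (Appendix A) and the CSQ-8 (Appendix C) are printed in English.

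**The concern.** The language rule for entry and the language of one outcome instrument do not match. A woman admitted on the strength of her English is due, at discharge, a 12-item Dutch form that also asks for free-text reasons for dissatisfaction and a choice of the three most important aspects. She may leave it blank, have it translated informally on the ward, or guess. The first loses her data. The other two produce answers from something other than the validated instrument.

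Patient satisfaction is part of the secondary objective in section 2.2, and the D-QUEST is the questionnaire that asks about the device. Section 9.5 provides only for counting missing data, so nothing later in the plan makes up for a group lost because of language. Answers not collected validly at discharge cannot be recovered afterwards.

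**Working it through.** No figure in the protocol bears on this point, so the check is a comparison of sections followed by a simple count.

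**Step 1. Who can enter.** Section 4.3 requires Dutch or English, and section 7.3.1 supplies patient information in both. Women who know only English are therefore meant to be eligible.

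**Step 2. What each patient instrument covers, and in which language it appears.**

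| Instrument | Timing | Subject | Language in the protocol |
|---|---|---|---|
| EQ-5D-5L and EQ VAS | Inclusion; 4 weeks after delivery | Health state on the day | English (Appendix A) |
| D-QUEST | Discharge | The device and its provision | Named as the Dutch version (7.1.2); Dutch text (Appendix B) |
| CSQ-8 | 4 weeks after delivery | Services received | English (Appendix C) |

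Only the D-QUEST asks about the device: its size, weight, adjustability, safety, durability, ease of use, comfort and effectiveness, and then its provision. Section 7.1.2 describes the EQ-5D-5L as assessing the effect of the eCTG on wellbeing, but its items ask about health in general. The CSQ-8 asks about the service. Neither can stand in for the D-QUEST.

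**Step 3. Whether another rule closes the gap.** The next bullet of section 4.3 excludes "Insufficient comprehension of instruction Nemo Remote® or patient information". It concerns the device instruction and the patient information, not the questionnaires. A woman who follows the instruction when it is explained in English passes it and still receives the Dutch form.

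**Step 4. How many women.** The protocol gives no share of participants who know English but not Dutch. Assume 2% to 10%, for illustration only:

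- 0.02 × 60 = 1.2, about 1 woman
- 0.10 × 60 = 6 women

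If their forms are left blank, 60 − 1 = 59 down to 60 − 6 = 54 usable forms remain, before any other loss. If the forms are completed without being understood, each is 1/60 = 1.7 percentage points of a response category, and six are 6/60 = 10 points.

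**Step 5. How the result is used.** Section 9.2.1 reports the D-QUEST as response categories from least to most satisfied. No test or decision depends on it.

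**The case against.** The strongest defence is that the appendices are specimens. Appendices A and C are printed only in English, yet Dutch-only women are eligible and will presumably receive Dutch versions; by the same reasoning an English QUEST may be intended although Appendix B shows Dutch. This has force against an argument built on the appendix alone. It does not answer section 7.1.2, where the Dutch version is part of the instrument's stated name and is assigned to all included patients. It is also fair that the D-QUEST is one descriptive secondary measure and that few women are likely to be affected.

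Four stronger readings are tempting, and the protocol does not support them.

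- *Language problems are scored as eCTG failures in the primary outcome.* No rule says this, and several provisions work against it. Section 4.3 excludes women who do not understand the device instruction. Section 7.3.2 has the investigator or a healthcare professional take each participant, inpatient or outpatient, through the whole procedure before the first recording. A reassuring but insufficient recording is repeated the same day before failure is declared. Section 7.1.2 records possible causes when poor signal leads to a switch. It is true that the failure definition does not separate user error from signal loss, but a language effect on the primary rate remains a conjecture.
- *No English Quick Start Guide exists.* This would be inferred from a file name. The protocol does not list an English guide; it does not say that none will be given.
- *Satisfaction data as a whole are invalid for these women.* The CSQ-8 and EQ-5D-5L are available in English, so only the D-QUEST is affected.
- *Eligibility should be limited to Dutch speakers.* Narrowing the study population to protect one descriptive questionnaire would be out of proportion.

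**Conclusion.** The mismatch stands, as a minor point confined to the D-QUEST. Sections 4.3 and 7.3.1 admit women who know only English; section 7.1.2 gives them the only device-satisfaction questionnaire in a language they may not read. As written, their D-QUEST data would be missing or unreliable.

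The size is unknown. About 1 to 6 of 60 women follows from an assumed share of 2-10%, which has no source in the protocol. The conclusion also assumes that section 7.1.2 is applied literally; if an English version is already planned, the protocol only needs to say so. The primary outcome, the sample size and the other questionnaires are unaffected.

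**What to change.** In section 7.1.2 and Appendix B, state that participants who do not read Dutch receive the English QUEST 2.0, and include that text. The reference list cites the Dutch version of the same QUEST 2.0; that an English text can be obtained is assumed here. Add one field to the case report form for the language in which the questionnaire was completed. In section 9.2.1, report the D-QUEST results with the number of respondents per language version. In section 7.3.2, confirm that an English Quick Start Guide is supplied and list it beside the NL file.

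The cost is one additional questionnaire version, one data field and, if it is not already in use, one guide. The downside is that the D-QUEST table pools two language versions, with probably only a handful of forms in English; showing the count per version makes this visible. The change helps only if it is in place before the women concerned reach discharge.
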